## 8. Conclusions

The present study intends to contribute with scientific knowledge regarding the progression of chronic DFUs in distressed patients, as well as to test the effectiveness of two stress reduction interventions for DFU healing, including the perspectives of patients and family caregivers. Thus, this study will surely have direct clinical relevance regarding DFU treatment and recurrence, with a significant impact on the QoL of patients and their family caregivers.

## Figures and Tables

**Figure 1 ijerph-19-08556-f001:**
[figure not shown]
Study design and CONSORT flow chart.

**Table 1 ijerph-19-08556-t001:** Schedule of enrollment, interventions, and assessments of the PSY-DFU study, following the Standard Protocol Items Recommendations for Interventional Trials (SPIRIT) guidelines.

TIMEPOINTS	Enrollment	Allocation	Pos-Allocation			Follow-Up
		T0	T0	T1	2 Weeks after T1	T2
Eligibility	X					
Informed consent	X					
Allocation		X				
INTERVENTIONS			[figure not shown]			
PMR + GI (TG1)						
H + GI (TG2)						
Control groups			[figure not shown]			
Active (ACG)						
Passive (PCG)						
ASSESSMENTS						
Sociodemographic data			X			
Health literacy			X			
Clinical data (PEDIS)			X	X		X
DFU evolution/healing ^a^			X	X		X
Impact of DFU on QoL			X	X		X
Mental and physical QoL			X	X		X
Perceived stress			X	X		X
Psychological morbidity			X	X		X
DFU representations ^a^			X	X		X
Blood pressure ^b^			X	X		X
Heart rate ^b^			X	X		X
Biochemical parameter			X	X		X
Inflammatory markers			X	X		X
Angiogenic markers			X	X		X
miRNAs			X	X		X
Immune cells			X	X		X
Semi-structured interviews					X	

QoL—quality of life; PMR + GI—progressive muscular relaxation with guided imagery; H + GI—hypnosis with guided imagery; ACG—active control group; PCG—passive control group; PEDIS—Perfusion, Extent, Depth, Infection, and Sensation; DFU—diabetic foot ulcer. ^a^ In T1 and T2, when the DFU is healed, the DFU progression and DFU representations are not assessed. ^b^ Blood pressure and heart rate are assessed before and after each intervention (PMR + GI and H + GI) and placebo (ACG) session.

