### 3.3. Measures of Primary Outcomes

Primary outcomes are DFU healing, physiological indicators of healing prognosis, DFU impact on QoL, and physical and mental QoL.

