### 3.4. Measures of Secondary Outcomes

Data will also be used to assess the following secondary outcomes: perceived stress, psychological morbidity, and DFU representations.

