#### 3.4.3. DFU Representations

Patient representations regarding the DFU will be evaluated through the Illness Perception Questionnaire—Brief (IPQ-B) [44], a self-report scale administered to participants.

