### 5.2. Data Analysis

The baseline data of the treatments and control groups will be compared using the chi-squared test for binary variables and the independent sample t-test for continuous variables. To prevent overestimating the impact of both interventions, an intention-to-treat approach will be assumed to evaluate the impact on the primary and secondary outcomes. The comparison between the treatment groups versus control groups over time (differences between and within) will be performed through mixed general linear models of analysis of variance for repeated measures. Effect sizes (Cohen’s d coefficient) will also be provided between T0 and T1, T1 and T2, and T0 and T2 to determine if the intervention shows any treatment effect. A significance level of 0.05 will be set for a two-sided test, and the 95% confidence interval will be calculated. In addition, time to complete wound healing and time to favorable healing prognosis (based on the wound size) will be estimated using survival analysis, specifically, single variable and multivariable Cox proportional hazard ratio regression models and Kaplan–Meier plots. All previous analyses will include the DFU stage at the baseline as a control variable. Other confounding clinical factors associated with the outcome variables will also be considered in the statistical analysis.

The data will be analyzed using the Rstudio, R version 3.6.2 (R Core Team, Vienna, Austria) and the SPSS statistics, v. 24.0 (IBM Corp., Armonk, New York, NY, USA).

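### The IPQ-B is not collected once the ulcer heals, so the intention-to-treat comparison promised for this secondary outcome rests at T1 and T2 on unhealed patients only

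*Protocol article*

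**What the plan says.** Section 3.4 of the protocol article names three secondary outcomes: "perceived stress, psychological morbidity, and DFU representations". Section 3.4.3 measures the third with the self-reported IPQ-B, and Table 1 schedules it at T0, T1 and T2.

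Section 5.2 states that "an intention-to-treat approach will be assumed to evaluate the impact on the primary and secondary outcomes". Treatment and control groups are compared over time with "mixed general linear models of analysis of variance for repeated measures", and Cohen's d is to be reported for T0 to T1, T1 to T2 and T0 to T2. The same section adds: "All previous analyses will include the DFU stage at the baseline as a control variable".

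Footnote a to Table 1 qualifies the schedule: "In T1 and T2, when the DFU is healed, the DFU progression and DFU representations are not assessed". The DFS-SF, SF-36, PSS and HADS rows, at the same visits, do not carry this footnote.

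Healing is itself a primary outcome. Section 3.3 reads: "Primary outcomes are DFU healing, physiological indicators of healing prognosis, DFU impact on QoL, and physical and mental QoL".

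**The concern.** Whether a patient has an IPQ-B score at T1 or T2 depends on an event after randomisation that the interventions are designed to bring about. If one arm heals more ulcers, its remaining IPQ-B sample is weighted towards harder cases, and the patients who did best have no score. The contrast at that visit is then not a comparison of the groups as randomised, although Section 5.2 presents it as one.

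The same footnote also covers the wound score, but there the gap can be filled: Section 3.3.1 defines a RESVECH score of zero as complete healing. No IPQ-B value follows from healing, so a healed patient cannot be scored by rule.

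Healing during treatment is not hypothetical. Section 7 reports that sessions stop when the ulcer has healed and that this contributes to low compliance.

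**Working it through.** The article gives no figure for the IPQ-B comparison and no healing rates, so there is nothing to reproduce and the size can only be shown under assumptions.

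**Inputs from the article.** 152 participants before dropout in four groups (Section 5.1), so 152/4 = 38 per arm.

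**Assumed.** Healing rates (control vs treated) of 20% vs 30%, 30% vs 45% and 40% vs 55%; a correlation r of 0.3 to 0.5 between ulcer severity and follow-up IPQ-B; IPQ-B with SD 1, higher meaning a more threatening view of the ulcer.

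**Model.** Latent severity U is standard normal, and a patient heals if U falls below the cut-off c that gives the assumed rate p. Among the unhealed, the mean of U is φ(c)/(1 − p). With no direct effect of treatment on IPQ-B, the treated-minus-control difference among unhealed patients is

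shift = r × (mean U of unhealed treated − mean U of unhealed control).

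The standard error of a pairwise contrast is roughly √(1/n₁ + 1/n₂), with n₁ and n₂ the unhealed patients out of 38.

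| Healed, control vs treated | Mean U, unhealed control | Mean U, unhealed treated | Shift, r = 0.3 | Shift, r = 0.5 | Scored of 38, control vs treated | SE |
|---|---|---|---|---|---|---|
| 20% vs 30% | 0.350 | 0.497 | 0.04 | 0.07 | 30 vs 27 | 0.27 |
| 30% vs 45% | 0.497 | 0.720 | 0.07 | 0.11 | 27 vs 21 | 0.29 |
| 40% vs 55% | 0.644 | 0.880 | 0.07 | 0.12 | 23 vs 17 | 0.32 |

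For example, 0.5 × (0.720 − 0.497) = 0.11 SD. The share without a score is the healing rate itself, 20 to 55% per arm.

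**Benefit omitted.** If healing improves IPQ-B by 0.5 to 1 SD, the all-randomised effect includes that gain times the difference in healing rates: 0.5 × 0.10 = 0.05 SD up to 1 × 0.15 = 0.15 SD. None of it appears in a contrast of unhealed patients, even if r = 0.

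**When the sign changes.** A simulation with a wider healing gap (30% vs 50%, r = 0.5, and a 0.5 SD gain on healing) varied the direct effect. Negative values favour treatment.

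| Direct effect | All randomised | Unhealed only | Unhealed only, adjusted for baseline IPQ-B |
|---|---|---|---|
| 0 | −0.10 | +0.15 | +0.11 |
| −0.10 | −0.20 | +0.05 | +0.01 |
| −0.20 | −0.30 | −0.05 | −0.09 |

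The sign reverses only while the direct benefit is smaller than the selection shift. With equal healing rates (30% in both arms, direct effect −0.10) all three estimates are −0.10. With r = 0 there is no selection shift.

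**The case against.** **Not asking about an ulcer that has gone is coherent.** The construct is the patient's view of the DFU, and how a reworded scale behaves after healing is undocumented. This stands, and it is why the fix offers a second route. It does not rescue the present text, because a measure defined only in unhealed patients cannot also be the intention-to-treat comparison of Section 5.2.

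**The planned model softens the problem.** Section 5.2 adjusts for baseline DFU stage and will consider other clinical confounders, which the calculation above omits. Stage removes the shift only as far as it predicts healing. In a likelihood-based mixed model, healed patients still contribute T0, and T1 if they healed later. The contrast at a given visit nevertheless rests on those unhealed then, and a repeated-measures ANOVA that deletes incomplete cases would lose the healed patients altogether.

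**The shift is small against the noise.** This is correct. At 38 per arm it is 0.17 to 0.38 standard errors, which would raise a two-sided 5% error rate to about 5.3 to 6.7%.

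**A reader might infer that an effective intervention will look harmful on illness perception.** The documents do not support that. They give no healing rates and no link between severity and IPQ-B. The imagery in Section 4.1.1 is aimed at how patients picture their ulcer, so a direct effect is plausible, and at −0.20 SD the simulation shows no reversal.

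**The analysis plan could settle this.** It could define the target of estimation, but it cannot recover answers that the schedule says will not be collected.

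**Conclusion.** The point holds as a conflict between footnote a and Section 5.2: both cannot stand for the IPQ-B. Under the assumed rates and correlations, unadjusted selection moves each follow-up contrast by about 0.04 to 0.12 SD against the better-healing arm, leaves 20 to 55% of patients per arm unscored, and drops any benefit that works through healing. The selection shift is zero if healing rates are equal or severity is unrelated to IPQ-B.

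A reversed sign requires unequal healing, a severity-IPQ-B link and a direct effect smaller than the shift. It is a possibility, not a finding. Nor does the footnote undermine the primary healing outcome, since the wound score is known once the ulcer has healed. One of three secondary outcomes is affected; it should be corrected, but it does not threaten the trial's main conclusions.

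**What to change.** Choose one of the following.

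1. **Collect it.** Remove DFU representations from footnote a, so that the IPQ-B is given at T1 and T2 whether or not the ulcer has healed, and analyse all randomised patients. The cost is one short questionnaire at visits where Table 1 already schedules the other scales. That healed patients attend those visits is inferred from the table, not stated. The wording needs adapting for a healed ulcer, and its comparability with the standard wording is undocumented. Section 7 suggests that the trial is under way, so a change now would mix patients with and without post-healing scores; the date of the change should be recorded.

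2. **Restrict the claim.** If the scale is judged not meaningful after healing, state in Section 5.2 that post-baseline IPQ-B is excluded from the intention-to-treat comparisons. Report it descriptively among patients unhealed at each visit, with the number healed per arm beside it. This costs only wording, but gives up a randomised comparison of illness perception at T1 and T2.

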#### 3.2.2. Clinical Information

Clinical data will be collected through the Clinical Questionnaire, developed specifically for this study, to be completed by the patients’ physician or nurse in the three assessment moments. This questionnaire asks about the type and duration of diabetes, complications associated with diabetes, diabetic foot type, DFU location and duration, concomitant treatment, ulcer healing time, and new DFUs. The clinical questionnaire also includes the Perfusion, Extent, Depth, Infection, and Sensation (PEDIS) classification system, proposed by the International Working Group of the Diabetic Foot, thus gathering information regarding the five most important categories to evaluate the DFU stage and progression [40].

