#### 3.3.1. Degree of DFU Healing

Wound healing is defined as the complete epithelization of the wound and is assessed through the RESVECH 2.0-PT [41], a useful and validated tool to monitor the progression of chronic wounds of any etiology through six main parameters: wound area, depth and involved tissues, wound margins, type of tissue in the wound bed, levels of exudates, and presence of signs of infection/inflammations. This questionnaire will be filled out by the participant’s physician or nurse at the end of consultations to monitor DFU progression. Scores range from 0 to 35, where zero indicates complete healing and 35 corresponds to the worse possible wound.

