#### 3.5.4. Time to Complete Wound Healing

This variable corresponds to the time interval (days) between the baseline assessment and the complete DFU healing.

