## 5. Statistical Analysis

### 5.1. Sample Size

Using Sakpal’s formula [49] and according to the descriptive results of the pilot study [50], considering the difference in the mean (1.93) and standard deviation (6) of the treatment versus passive control groups, with a statistical power of 80% and a statistical significance level of 5%, a definitive RCT will require 152 participants. Considering a dropout rate for intervention sessions of 11%, a definitive RCT with four groups will require a sample size of 169 participants, with 42 patients per group [49].

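### Table 1 stops scoring the primary healing outcome once the ulcer has healed, and the plan does not say that healed patients enter the RESVECH analysis as 0

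*Protocol article*

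**What the plan says.** Table 1 of the protocol article attaches footnote a to two rows, the one for DFU evolution and healing and the one for DFU representations. The footnote reads: "In T1 and T2, when the DFU is healed, the DFU progression and DFU representations are not assessed".

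Section 3.3 lists DFU healing among the primary outcomes. Section 3.3.1 gives its definition and instrument: "Wound healing is defined as the complete epithelization of the wound and is assessed through the RESVECH 2.0-PT". It also fixes the value of a healed wound: "Scores range from 0 to 35, where zero indicates complete healing and 35 corresponds to the worse possible wound".

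Section 5.2 says that "an intention-to-treat approach will be assumed to evaluate the impact on the primary and secondary outcomes", and that groups will be compared over time with "mixed general linear models of analysis of variance for repeated measures". It gives no value for an ulcer that has healed and is no longer rated.

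Healing is also recorded by other routes. The Clinical Questionnaire in Section 3.2.2, completed at all three assessments, covers "concomitant treatment, ulcer healing time, and new DFUs". Section 3.5.4 defines time to complete healing: "This variable corresponds to the time interval (days) between the baseline assessment and the complete DFU healing".

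**The concern.** The scale has a defined value for the best possible result, yet the assessment schedule tells staff not to record the scale when that result is reached. Followed as written, a patient whose ulcer has closed has no RESVECH entry at that visit, and the reason for the gap is the outcome itself. Section 7 says that the intervention ends when an ulcer heals completely, so such patients are expected during the treatment period.

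Neither usual reading of the Section 5.2 model repairs a blank cell. A classical repeated-measures ANOVA drops the patient. A likelihood-based mixed model keeps the patient but predicts the missing visit from earlier, unhealed scores. In both cases the zero is lost. The comparison between arms then conditions, wholly or partly, on a post-randomisation result, which is not what intention to treat promises. What is at stake is the treatment contrast on a primary outcome.

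Two related gaps follow. There is no rule for an index ulcer that heals by T1 and has reopened by T2. For DFU representations, a secondary outcome measured with the IPQ-B, the article defines no value for a healed ulcer at all.

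**Working it through.** **Yardstick.** Section 5.1 gives a difference of 1.93 and an SD of 6. With 80% power and two-sided 5%, the standard two-mean formula gives 2 × [6 × (1.960 + 0.842) / 1.93]² = 151.7, that is 152 per group. Section 5.1 uses 152 as a trial total. That is a separate matter and nothing below depends on it. Section 5.1 does not name the scale behind 1.93 and 6, so using them as RESVECH values is an assumption.

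**Assumed input.** The article gives no healing proportion. Control healing is varied from 10% to 50%.

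**Model A: floored normal.** A latent score is normal with mean m and SD 6. Ulcers at or below 0 are healed and score 0.

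- Healed share: h = Φ(−m/6)
- Mean with healed scored 0: F(m) = m·Φ(m/6) + 6·φ(m/6)
- Mean among the unhealed: U(m) = F(m) / (1 − h)

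The treatment mean is chosen so that F differs by exactly 1.93. For 10% control healing:

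- Control: m = 7.689, F = 7.973, U = 7.973 / 0.900 = 8.859
- Treatment: m = 5.450, h = 0.182, F = 6.043, U = 6.043 / 0.818 = 7.387
- Difference with healed scored 0: 7.973 − 6.043 = 1.93
- Difference among the unhealed: 8.859 − 7.387 = 1.47, or 76%

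| Control healed | Treated healed | Healed = 0 | Unhealed only | Share kept |
|---|---|---|---|---|
| 10% | 18% | 1.93 | 1.47 | 76% |
| 20% | 34% | 1.93 | 1.37 | 71% |
| 30% | 50% | 1.93 | 1.36 | 71% |
| 40% | 67% | 1.93 | 1.44 | 75% |
| 50% | 85% | 1.93 | 1.68 | 87% |

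Shares are taken from unrounded values.

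**Three-visit simulation.** This used T0, T1 and T2 with baseline adjustment, analysed visit by visit, with healed ulcers staying healed. With about 17%, 34% and 50% of controls healed by T2, the T2 difference (healed = 0 against unhealed only) was 2.34 against 1.82, 1.81 against 1.44, and 1.31 against 1.17. The shares kept are 78%, 80% and 89%. With no treatment effect the unhealed-only difference was −0.01, so there was no bias.

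**Other patterns of effect (assumed figures).**

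- Treatment changes only the chance of healing: 16 more healed per 100, unhealed mean 12 in both arms. True difference 0.16 × 12 = 1.92; unhealed-only difference 12 − 12 = 0.
- Extra healing comes from the mildest ulcers: control 30% healed, unhealed mean 10, so F = 0.70 × 10 = 7.0. Treatment heals a further 15% whose mean would have been 4, so F = 7.0 − 0.15 × 4 = 6.4. True difference 0.60; unhealed-only difference 10 − 6.4/0.55 = −1.64.
- Treatment lowers unhealed scores by 2.5 with 20% healed in both arms: true difference 0.80 × 2.5 = 2.0; unhealed-only difference 2.5.

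The result can therefore be attenuated, null, reversed or enlarged.

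**The case against.** The strongest reply is that the footnote says when a form is not repeated, not how the value is analysed. The scale itself supplies the value 0, so declining to re-rate a closed wound is compatible with carrying a known zero, and the intention-to-treat statement points that way. Section 3.3.1 has RESVECH completed at the end of consultations, so the visit at which healing is established may already yield the 0. Healing time and new ulcers are collected at every assessment, the clinical data row with PEDIS carries no footnote a, and healed patients count as events in the survival analysis. The coding of a healed state may also be set out in an analysis plan that is not shown.

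Much of this stands. A reader might infer that healed patients are excluded from the primary analysis. The article does not say so, any more than it says that they are entered as 0. A reader might also infer that the effect is biased towards zero. That needs both blank cells and a particular pattern of effect, and the documents establish neither. The case in which the whole effect vanishes uses figures chosen to multiply to about 1.93.

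What remains is that the footnote is a stated data-collection rule, not an omitted detail, and it sits badly with Section 3.3.1. That zeros could be reconstructed is not a rule that they will be. Time to healing is listed among the other outcomes in Section 3.5 and does not replace the primary score. Collecting new ulcers and PEDIS at T2 helps with reopened wounds, but the article does not say whether a reopened index ulcer counts as new.

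**Conclusion.** The point holds as a conditional one. The protocol stops recording a primary outcome at the moment that outcome takes its best value, and it does not say that the value is entered as 0. If the cells are left blank, the repeated-measures comparison is restricted to, or extrapolated from, unhealed ulcers, contrary to the stated intention-to-treat approach.

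Attenuation is plausible: about 71% to 87% of a 1.93-point difference is kept in Model A. That range rests on the floored-normal shape, SD 6, the assumed healing shares and the reading of 1.93 as RESVECH points. It is an illustration and not an estimate for this trial. The harm is a distorted effect size and not a false positive, since no bias appears when treatment has no effect. If healed ulcers are scored 0, this source of distortion disappears.

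For DFU representations the restriction is firmer. The T1 and T2 comparison covers unhealed patients only, and the article defines no value that would fill the gap.

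**What to change.** - Limit footnote a in Table 1 to DFU representations (IPQ-B).
- Record index-ulcer status at T1 and T2 for every patient, including those already healed.
- Enter RESVECH = 0 when the ulcer is fully epithelialised, and score it normally if it has reopened.
- State in Section 5.2 that healed patients stay in the RESVECH analysis with score 0.
- Note in Section 5.2 that any IPQ-B comparison at T1 or T2 is restricted to unhealed patients and should be interpreted accordingly.

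The cost is one footnote, two sentences in Section 5.2 and one status item at visits already scheduled. For patients already assessed, zeros can be filled in from the recorded healing time, with a check for reopening at T2.

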## Data Availability

Not applicable.
